##### Data management

2.3.7.5

All original data will be recorded in the CRF severally. The completed CRF, after signed by the direct investigators, will be transferred to the head investigator ([name]). Data entry will be doubly performed by 2 investigators using the Excel 2010. Head investigator and research nurse who is responsible for data collection, sort, and dataset construction have the right of accessing to the final trial dataset. More importantly, all process associated with data access and analysis will be supervised by the Clinical Research Ethics Committees of Chongqing University Cancer Hospital & Chongqing Cancer Institute & Chongqing Cancer Hospital.

##### Statistical analysis

2.3.7.6

In this study, we will adopt intent-to-treat (ITT) and per-protocol (PP) method to analyze all data. Demographic and clinical characteristics will be summarized with means, medians, and standard deviations. To assess differences between groups, data will be analyzed with Mann–Whitney *U*-test, Student's *t* test and Chi-square test according to the variables evaluated. Differences between groups regarding the bowel preparation efficacy will be analyzed with the Chi-square test. We will perform the subgroup analyses according to the indication for colonoscopy and previous history of colonoscopy. It is noted that all statistical analyses will be conducted with 2-tailed test, and *P* values of < .05 will be considered as considered significant. All statistical analyses will be performed by blinded professional statisticians with SPSS ver. 17.0 for Windows (SPSS Inc., Chicago, IL).

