#### Recruitment, randomization, and blinding

2.3.4

The day before colonoscopy, investigators who have been trained for the study and are authorized by the principal investigator will assess candidates according to the inclusion and exclusion criteria. After eligible patients were identified, the written informed consents will be obtained from the eligible patients, their next of kin or legal representatives. At the phase, the investigators will also collect demographic and clinical characteristics data of all eligible patients, which includes sex, age, body weight, body mass index, reasons for colonoscopy, previous colonoscopy history, and comorbidity such as hypertension, diabetes mellitus, and cardiovascular disease.

All recruited patients will be randomly assigned to receive one of the 3 preparation regimes including 3 L PEG, combination of 2 L PEG and 30 mL castor oil, and combination of 1 L PEG, 30 mL castor oil, and 5 g ascorbic acid. We will generate the random sequence by using SPSS 17.0 software, and the random sequence will be sealed in opaque envelope. An independent research nurse will be designated to random all patients into 3 different groups according to the random sequence.

In order to eliminate the risk of bias as much as possible, the endoscopists will be blinded except the research nurse who conducted the randomization procedure during examine period. Moreover, we will also blind the biostatistician.

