##### Secondary outcomes

2.3.7.2

We will also measure the first defecation time (the endoscopists record the time of first defecation after digesting regime), the total number of defecation (the direct investigators record the number of defecation before performing the colonoscopy), the time of cecal intubation (the endoscopists record the time of starting procedure to reaching ileocecal part), detection rate of polyp and adenoma (the number of polyp and adenoma during colonoscopy), tolerance to recommended regime (the research nurse ask the patients answering the questioner with a 4-point scale), and willing to repeat the same bowel regime (the research nurse instruct the patients to answer whether they will select the same regime to perform the bowel preparation) as the secondary outcomes.

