##### Laboratory tests

2.3.7.4

The 2 mL blood sample will be collected before and after the bowel preparation. These all samples will be transferred to clinical laboratory of Chongqing University Cancer Hospital & Chongqing Cancer Institute & Chongqing Cancer Hospital in order to know and further compare the change of all electrolytes such as serum sodium and potassium. All blood samples will be probably handled after analyzed in accordance with Chinese guidelines of Good Clinical Practice (GCP).

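### Outcomes are compared unadjusted although baseline factors are collected: valid, but some precision is given up, mainly for polyp and adenoma detection and very little for the primary outcome

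*Protocol article*

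**What the plan says.** Under Recruitment, randomization, and blinding, the investigators collect baseline data at the consent stage, the day before colonoscopy: "sex, age, body weight, body mass index, reasons for colonoscopy, previous colonoscopy history, and comorbidity such as hypertension, diabetes mellitus". The text places this before assignment. The randomisation paragraph in the same section begins "We will generate the random sequence by using SPSS 17.0 software", goes on to opaque envelopes, and names no stratification factor.

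Under Statistical analysis, the primary outcome is handled as follows: "Differences between groups regarding the bowel preparation efficacy will be analyzed with the Chi-square test". Other comparisons use the Mann–Whitney test, the t test or chi-square, chosen by type of variable. No regression model or covariate is mentioned. Two of the baseline factors reappear once, for a different purpose: "We will perform the subgroup analyses according to the indication for colonoscopy and previous history of colonoscopy".

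Under Secondary outcomes, lesion detection is given as "detection rate of polyp and adenoma (the number of polyp and adenoma during colonoscopy", with no expected rate. Electrolytes are a separate matter, because the Laboratory tests section already compares their change from the sample taken before preparation.

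**The concern.** The trial pays to collect baseline factors on every patient and uses them only for description and two subgroup splits. A subgroup split divides a small sample further. Putting the same factor into the main comparison as a covariate would sharpen the overall estimate with data already in hand. If a factor predicts the outcome, an unadjusted comparison leaves that predictable variation in the error term.

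There is a second, smaller point. With no stratification described, a visible imbalance in indication or previous colonoscopy between some two arms would not be unusual. The article states no advance analysis that accounts for one, and choosing covariates after seeing the imbalance would be open to criticism.

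**Working it through.** **Inputs from the protocol article.** Expected adequate preparation is 85%, 90% and 95%; the total is 255 before dropout and 282 enrolled; power is 80%; tests are two-sided at 0.05. Equal arms of 85 (94 enrolled) are assumed.

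**Inputs not in the article (assumptions).** Detection rate 25–40%; C-statistic of the baseline factors 0.65–0.75 for detection and 0.60–0.70 for preparation; prevalence of a baseline factor 40%.

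**Step 1: the plan's own sample size.** The mean rate is 0.90. The squared effect size of the three-arm chi-square test is [(0.05² + 0 + 0.05²)/3] / (0.90 × 0.10) = 0.0185, so w = 0.136. With 255 patients the noncentrality is 255 × 0.0185 = 4.72, which on 2 degrees of freedom gives 48% power; 282 patients give 52%. The same test needs 521 patients for 80%. The stated 255 is therefore not reproduced. This is a separate and larger problem, and it matters here because it shows what adjustment cannot mend.

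**Step 2: variance removed by adjustment.** In large samples, the variance of an adjusted risk difference falls by the share of outcome variance the covariates explain. With a logistic model and a normally distributed linear predictor scaled to give the stated C-statistic, that share is R² = Var(p) / [π(1 − π)], where π is the overall rate. The equivalent number of extra patients is 282 × [1/(1 − R²) − 1].

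| Outcome | C | R² | Extra patients on 282 |
|---|---|---|---|
| Detection 25% | 0.65 | 0.054 | 16 |
| Detection 25% | 0.70 | 0.098 | 31 |
| Detection 25% | 0.75 | 0.156 | 52 |
| Detection 40% | 0.65 | 0.067 | 20 |
| Detection 40% | 0.70 | 0.118 | 38 |
| Detection 40% | 0.75 | 0.184 | 64 |
| Adequate 90% | 0.60 | 0.012 | 3 |
| Adequate 90% | 0.65 | 0.028 | 8 |
| Adequate 90% | 0.70 | 0.054 | 16 |

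**Step 3: simulation.** With 85 per arm and 3,000 runs per setting, the unadjusted chi-square test was compared with a logistic likelihood-ratio test adjusted for one prognostic score (odds ratio per SD of 1.0, 1.65 and 2.72).

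- Unadjusted type I error was 4.9–5.3% for preparation and 4.6–5.0% for detection, whatever the strength of the score.
- Primary outcome, power unadjusted then adjusted: 49.2% to 52.3%, 47.1% to 51.2%, and 48.7% to 55.2%. The first gain, about 3 points, comes from a score with no prognostic value. It reflects a slightly liberal adjusted test (5.7–6.2% error under the null). The real gain is about 1–3 points.
- Detection at assumed rates of 20%, 30% and 40%: 72.8% to 73.2%, 73.9% to 76.4%, and 71.5% to 80.2%, a gain of about 0–9 points.
- A separate simulation of the standardised risk difference gave roughly 9–13% less variance for detection and about 3% for the primary outcome, with error rates close to those of the unadjusted tests.

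**Step 4: chance imbalance.** For a factor with 40% prevalence and three arms of 94, the largest gap between any two arms is at least 10 points in about 33% of simulated trials (19% at 20% prevalence, 35% at 50%).

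**Step 5: what the primary model can carry.** Expected inadequate preparations are 85 × (0.15 + 0.10 + 0.05) = 25.5. Two arm terms and two single-term covariates make four parameters, about 6 events each (25.5/4). Six covariates would make eight parameters, about 3 events each (25.5/8).

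**The case against.** The strongest reply is that nothing here is wrong. A chi-square test of a binary outcome in a randomised trial is valid, and its error rate already allows for chance imbalance. A reader might infer from the imbalance figure that the unadjusted result is biased. The documents do not support that, and the type I error in Step 3 contradicts it. Imbalance can move a single estimate, but usually by little: if a factor shifted adequacy by 10 points (assumed), a 10-point imbalance would move the arm difference by 0.10 × 10 = 1 point. The standard error for 85% versus 90% with 94 per arm is about 4.8 points. This part of the reply stands.

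It also stands that prognostic strength is unknown. The article gives no detection rate and does not say that age, sex or indication predict lesions. Naming factors for subgroups shows interest in differing effects, not evidence of prognostic value. The exclusion criteria already remove patients at high risk of failed preparation, which may leave less for the remaining factors to explain.

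A further objection is that an adjusted analysis could sit in an analysis plan that is not shown. That limits the force of the point but does not remove it: the article is not silent on method, and every test it names is unadjusted.

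Finally, replacing the primary chi-square test with a model on about 25 events would exchange a stable test for a less stable one, for a very small gain. That objection is accepted, and the proposal leaves the primary test alone.

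**Conclusion.** The point holds as a modest matter of efficiency. The tests named are valid. They forgo precision that the collected data could supply: about 5–18% of variance for polyp and adenoma detection, and about 1–5% for the primary outcome. These figures rest on the assumed detection rates and C-statistics, on detection being analysed as a yes/no result per patient, and on a large-sample approximation. If the factors predict little, the gain is close to nil.

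Two stronger readings should be resisted. The first is that adjustment is needed to make the primary comparison sound; it is not. The second is that adjustment would rescue the trial's power; the primary comparison stays at about 50–55% with or without it.

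**What to change.** Add a few sentences to the Statistical analysis section, fixed before unblinding.

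- **Polyp and adenoma detection.** Define each as detected or not per patient. Compare each castor oil arm with 3 L PEG by a logistic model with arm, age, sex and indication, reported as a standardised risk difference with its confidence interval.
- **Primary outcome.** Keep the chi-square test as primary. Add a supportive standardised risk difference adjusted for at most indication and previous colonoscopy, each coded as a single term.

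No new data, visits or patients are needed. The price is that the short covariate list, and the coding of indication, must be settled in advance and not altered after the arms have been compared. The shortfall in power shown in Step 1 needs its own remedy.

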## Discussion

3

Although several advanced treatments for CRC have been developed, CRC remains one of the common cancers worldwide.^[1]^ Although many noninvasive tests such as fecal immunochemical test, fecal occult blood test, and CT colonography are available,^[33]^ colonoscopy has been used a preferred method to early diagnosing CRC and treating gastrointestinal lesions,^[3]^ and the issued data suggested that the colonoscopy was associated with the decreased mortality of CRC.^[27]^ It is noted that, however, the inadequate bowel preparation will significantly decrease the effectiveness and safety of this given procedure.^[6]^ A numerous of regimes such as PEG, NaP, and sodium picosulphate with magnesium citrate have been developed to clean colon before colonoscopy,^[34]^ but the effectiveness of all these regimes are not still satisfactory.^[35]^ And thus, it is essential to develop novel bowel preparation regime.

Some published evidences suggested that 30 mL castor oil has the potential of enhancing colon cleans compared to NaP.^[12]^ Moreover, evidence also demonstrated similar laxative efficacy between castor oil and bisacodyl.^[15]^ However, it is unclear if 30 mL castor oil may enhance the potential of PEG prior to colonoscopy.

So we design the randomized, double-blind, single center with three-arm design to test whether 30 mL castor oil may enhance the potential of 2 L PEG and combination of 30 mL and 5 g ascorbic acid may halve the required volume of PEG. The results of the trial will influence evidence based decision making for bowel preparation regimen prescriptions as it will be fundamental in providing reliable recommendations for bowel preparation regimens before colonoscopy.

## Ethics and dissemination

4

The study protocol has been approved by the Clinical Research Ethics Committee of the Chongqing University Cancer Hospital & Chongqing Cancer Institute & Chongqing Cancer (2017[107]). In order to guarantee the right of all eligible patients during the study period, we will strictly follow the Declaration of Helsinki and Chinese guidelines of Good Clinical Practice.

During the screening and recruitment, the investigators must explain to each eligible candidate in detail the purposes, procedures, and potential benefits and risks of the study. At the same time, the investigators must also let every potential patient know that he/she has the right to withdraw consent at any time during the study period. We will give sufficient time to each potential patient so that the decision of participating in the clinical trial can be rationally made. Every patient or the authorized surrogate of the patient must give the written informed consent before considered for enrolment in the study. All written informed consents will be kept as a part of the clinical trial documents.

All investigators will be informed that personal information provided by every patient will only be used to research. These all information will not be used to achieve other purposes which are not anticipated in the study. Certainly, all process will be performed according to the Chinese guidelines of Good Clinical Practice. Results of the study will be submitted to peer-reviewed academic journals, and will be presented at national and international conferences.
